### Sample size

We will use machine learning algorithms to predict the primary end point (i.e., the change in FM-UE 90 days after the stroke event compared to the initial FM-UE, see definition under “Outcomes”) as a function of the primary data set and the rehabilitation data set detailed in Tables 2, 3. Model development will start once 50 patients have been reached and continue throughout the study. To cope with the dimensionality of the problem, we will use lasso-regularized linear regression to select a sparse subset of the potentially correlated features. We will use a nested-cross validation setup to tune the regularization strength via the 1SE-rule [29] and obtain estimates of the fraction of the explained variance of the total variance in the primary end point on data not seen during model training. Due to the exploratory nature of the project and the complex models involved, a precise sample size calculation is not feasible.

**Table 2 Tab2:** Timeline for collecting the primary data set in the university hospital and other study sites

		Clinical data	Imaging data	Electrophysiological data	Laboratory data
0–24 h		NIHSS*			Blood sample*
25–48 h		mRS*	MRI* or CT*		
49–96 h		SAFE score		EEG	
				MEP	
		Grip strength			
		FMA			
		ARAT			
		BI*			
		Bells test			
		AST			
		BDI			
		SS-QOL scale			

Tests marked with * are part of the usual stroke work-up

Abbreviations: *NIHSS* National Institute of Health Stroke Scale, *mRS* modified Rankin Scale, *SAFE* Shoulder Abduction Finger Extension score, *FMA* Fugl-Meyer Assessment, *ARAT* Action Research Arm Test, *BI* Barthel Index, *MRI* magnetic resonance imaging, *CT* computed tomography, *Aphasie-Schnelltest, AST* aphasia quick test, *BDI* Beck’s Depression Inventory, *SS-QOL* Stroke-Specific Quality Of Life scale, *EEG* electroencephalography, *MEP* motor evoked potential

**Table 3 Tab3:** Overview over complete data collection

Location	Time point	Data set
University hospital of Tübingen, other recruiting study sites	Day 1–4 after stroke	Primary data set (see Table 1)
Rehabilitation hospital	On admission	Rehabilitation data set: FM-UE, BI and mRS
	Every 14 days during the stay and on discharge	• FM-UE, BI, mRS and questionnaire to capture soft influencing factors • Number, duration and type of neurorehabilitative treatments
University hospital	Day 90 after stroke	FM-UE, ARAT, BI, mRS, SS-QOL scale

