### Statistical methods

Statistical methods for primary and secondary outcomes.

Only those participants will a complete data set (including the 90 days follow-up examination or a lethal outcome) will be included in the statistical data analysis. Previous studies suggested that the FM-UE endpoints (i.e., the change in FM-UE 90 days after the stroke event compared to the initial FM-UE, see definition under “Outcome”) or the recovery trajectories of FM-UE scores can be clustered into 3 to 5 subgroups [4, 40]. We will first use time series clustering methods such as mixture of Gaussian processes [41] to identify such subgroups, then use the inferred cluster labels to build a classifier using lasso-regularized logistic regression to predict the group membership of the patient as a function of the primary data set and rehabilitation data set detailed in Tables 2, 3. The lasso regularization can automatically select a sparse subset of the significant features, reducing the dimensionality of the feature space and potentially the sample size required. We will use a nested-cross validation setup to tune the regularization strength via the 1SE-rule [29]. We can then use the Gaussian process model of the respective group to predict the primary endpoint and obtain estimates of the fraction of the explained variance of the total variance in the primary end point on data not seen during model training. If the linear model proves insufficient or unsatisfying, we will resort to non-linear regression models such as Generalized Additive Models (GAMs), which allow flexible nonlinear transformations of individual features of pairs of features [42]. Models for secondary endpoints will be built as well.

Interim analyses are not planned since this an observational study without interventions. No further analyses are planned apart from what is described under statistical methods for primary and secondary endpoints. Biobanking of blood samples will allow future (not yet planned) analyses of the relation of blood markers to stroke rehabilitation outcome.

Methods in analysis to handle protocol non-adherence and any statistical methods to handle missing data.

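### Two unreconciled analyses of the primary endpoint, plus a performance-triggered model switch outside the described nesting, may make the reported explained variance slightly optimistic

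*Protocol article*

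**What the plan says.** The primary endpoint is the change in FM-UE at 90 days as a percentage of the initial impairment. The protocol article describes its analysis in two places.

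- **Sample size section.** The endpoint is modelled directly: "we will use lasso-regularized linear regression to select a sparse subset of the potentially correlated features". On timing: "Model development will start once 50 patients have been reached and continue throughout the study".
- **Statistical methods section.** The route has three steps. First, "We will first use time series clustering methods such as mixture of Gaussian processes". Then the inferred labels are used to "build a classifier using lasso-regularized logistic regression to predict the group membership of the patient". Finally, "We can then use the Gaussian process model of the respective group to predict the primary endpoint".

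The Statistical methods section then gives a fallback: "If the linear model proves insufficient or unsatisfying, we will resort to non-linear regression models", with generalised additive models (GAMs) as the example. It says that nothing beyond the analyses it describes is planned, and on interim looks: "Interim analyses are not planned since this an observational study without interventions".

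Both sections use nested cross-validation. Both name tuning of the lasso penalty by the 1SE rule as the choice made within it, and both report the share of endpoint variance explained on data not used in training. The Trial design section calls the framework exploratory.

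**The concern.** Three things do not fit together.

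1. **No single primary result.** The two sections lead to two different explained-variance estimates for one endpoint. Neither refers to the other. Read literally, the statement that no further analyses are planned would exclude the regression in the Sample size section.
2. **A switch that depends on performance.** Whether a model is good enough is most naturally judged on how well it predicts, and the only performance measure named is the explained variance to be reported. No metric, threshold or time is given. The reference to a linear model also fits the Sample size regression better than the classifier and Gaussian processes described just before it.
3. **Wording on looks at the data.** Modelling the endpoint from the 50th patient onward requires outcome data during the study, which sits awkwardly beside the statement that no interim analyses are planned.

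The aim is to predict motor outcome more accurately than is now possible, so the explained variance is the main result. Cross-validation protects it only against choices made inside the loops. A model family picked afterwards on the outer-loop estimate is not covered.

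**Working it through.** The article gives no expected explained variance, power or sample size formula, so there is no figure of the plan's own to reproduce. The check has two parts.

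**Which choices are nested**

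| Choice | Where described | Placed inside the nested cross-validation? |
|---|---|---|
| Lasso penalty | Both sections | Yes |
| Direct regression or cluster route | One in each section | Not stated |
| Switch to GAMs | Statistical methods | Not stated; depends on performance |
| Number of clusters (earlier studies suggest 3 to 5) | Statistical methods | Not stated |

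Three model families therefore compete for one endpoint.

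**Size of the optimism if the best outer-loop R² is the one reported**

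Inputs: n = 200 (the recruitment target) and k = 3 families, both from the article. Assumed, because the article gives no values: all three families have the same true R² of 0.40, and their residuals correlate at ρ = 0.8 to 0.9.

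With normal residuals, the squared residuals of two families correlate at ρ². The expected excess of the best R² over the common true value is about

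(1 − R²) × √(2/n) × √(1 − ρ²) × E[max of k standard normals], with E[max of 3] ≈ 0.846.

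- (1 − 0.40) × √(2/200) = 0.60 × 0.10 = 0.060.
- ρ = 0.8: 0.060 × √0.36 × 0.846 = 0.060 × 0.600 × 0.846 = 0.030.
- ρ = 0.9: 0.060 × √0.19 × 0.846 = 0.060 × 0.436 × 0.846 = 0.022.

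For scale, SE(R²) = √(4 × 0.40 × 0.60² / 200) = 0.054, a 95% half-width of 1.96 × 0.054 ≈ 0.105. The excess is roughly a fifth to just under a third of that.

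**Wider assumptions.** A second approximation is SE(R²) × √(1 − r) × 0.846, where r is the correlation between the R² estimates themselves.

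- Largest case, R² = 0.3 and r = 0.5: 0.054 × 0.707 × 0.846 = 0.032.
- Smallest case, R² = 0.7 and r = 0.95: 0.035 × 0.224 × 0.846 = 0.007.

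**Unequal families.** Equal performance is the unfavourable case. A small simulation (19 to 29 replicates per setting, 40 features, nested 5-fold cross-validation with the 1SE rule) used simplified versions of the three routes. At n = 200 with true R² 0.5, the mean R² was 0.391 (linear), 0.142 (cluster) and 0.375 (non-linear). The mean of the largest was 0.393, which is 0.002 above the best single route and 0.005 above the selected route's own mean. At n = 50 the same two differences were 0.019 and 0.054.

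**Early model building.** The first 50 patients are 50/200 = 25% of the target. Modelling them early does not by itself inflate the final estimate. It could do so only if pipeline choices made on them are kept and they are then scored again in the final cross-validation. The article does not say whether that happens.

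**The case against.** The strongest reply is that optimism is not shown. A reader might infer that the reported explained variance will be the best of several looks and is therefore biased. The article does not say so. It describes a sequence with a fallback, and each estimate is meant to come from data not used in training. Bias needs the further step of choosing on the reported estimate, which the article neither requires nor excludes. This objection stands, so the conclusion is that the estimate may be optimistic, not that it is.

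Other points that stand:

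- **Interim statement.** A reader might see a flat contradiction. The reason given is the observational design, which suits the usual meaning of an interim analysis as a look that guides study conduct. Model building on accruing data is disclosed openly. No hypothesis test or stopping rule is described, so no type I error is at stake. The mismatch is one of wording.
- **Imputation.** It might be counted among the choices made on reported results. The missing-data paragraph says algorithms are first tested on artificial data, before work on participant data, so the text does not support that.
- **Number of clusters.** The article cites a range from earlier studies and does not say that the number is chosen on predictive performance.
- **Exploratory framework and condensed article.** A full protocol is said to be public and an analysis plan may exist. Details such as a code freeze can sit there.

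This last point does not remove the core. Two different analyses of one endpoint and a switch worded to depend on performance are what the article itself states, not details it leaves out. An exploratory label also does not make a performance estimate unbiased.

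**Conclusion.** The point holds in a limited form. The Sample size and Statistical methods sections describe different analyses of the same primary endpoint without naming one as primary. The move to non-linear models depends on performance, has no criterion, and lies outside the nesting as described.

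If the family is chosen on the same cross-validated R² that is then reported, the expected excess at n = 200 is about 0.02 to 0.03. This assumes three equally good families, a true R² of 0.40 and residual correlations of 0.8 to 0.9; wider assumptions give 0.007 to 0.032. If one family clearly dominates, the excess is near zero. It would be larger with fewer analysed patients, and could be larger if clustering on trajectories that include day 90 were done outside the outer folds. The article is silent on that, and it was not quantified.

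The numerical bias is modest. The missing primary analysis is the more important defect, and both are cheap to repair.

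**What to change.** 1. Describe one primary pipeline, in the same terms, in the Sample size and Statistical methods sections.
2. Replace the fallback sentence. Choose the model family (lasso linear, cluster mixture, GAM) and the number of clusters inside the inner loop, and refit the clustering within each outer training fold. The outer loop then scores the whole procedure once, and selection adds no excess by design.
3. Reword the sentence on interim analyses to say that models are developed on accruing data from the 50th patient, and that no interim decisions about study conduct are made.

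Reporting performance separately in later-enrolled patients is optional; that estimate would be imprecise because the group is small.

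The cost is wording, computing time and a possibly slightly lower reported R². No additional patients or measurements are needed.

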### Participant timeline

In the first 96 h after stroke onset the primary data set (see below) is acquired by the University Hospital of Tübingen, or one of the other cooperating acute-care hospitals.

0–24 h: The patients will be screened for participation, written informed consent will be obtained, the first clinical tests will be conducted adapted to the patient’s fitness, and a blood sample (part of the usual stroke workup) is collected.

25–48 h: Neuroimaging (magnetic resonance imaging (MRI) or computed tomography (CT)) will be conducted and further clinical tests adapted to the patient’s fitness will be performed.

49–96 h: Adapted to the patient’s fitness, clinical tests, EEG and motor evoked potentials (MEPs) will be performed.

After completion of acute stroke treatment, participants are transferred to collaborating neurorehabilitation facilities. There, the rehabilitation data set is collected:

On admission: FM-UE, BI and mRS.

During the stay:At intervals of 14 days: FM-UE, BI and mRSnumber, duration and type of neurorehabilitative treatments

On discharge:FM-UE, BI and mRS

Final examination:

After 90 days the final follow-up examination is carried out. The following data is collected: FM-UE (primary endpoint), ARAT, BI, mRS, SS-QOL scale (secondary endpoints).

There are no interventions planned in this observational study. All participants are treated according to the current guidelines, the same way they would have been treated outside of this study.

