Before model development with participant data will be started, algorithms will be tested with artificial data sets including sets with missing data. Effective algorithms such as nearest neighbors imputation [43] or multivariate imputation [44] on simulated data-sets with missing data will be used as candidate-algorithms for analysis of the empirical data.

Plans to give access to the full protocol, participant level-data and statistical code.

The study protocol is already accessible to the public on the website of the primary study center (https://hih-tuebingen.de/en/research/neurology-and-stroke/research-groups-and-foci/brain-networks-and-plasticity/) [45]. The statistical code will be available in GitHub. Participant-level data can be provided anonymously.

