## Discussion

The primary objective of the present study is to identify markers in the acute phase of stroke predicting recovery of UE motor function and determine the most suitable neurorehabilitative treatment in a given patient based on the acquired data sets using machine learning algorithms.

Although we aim to include the whole spectrum of stroke patients (with a FM-UE ≤ 50 points, indicating a relevant deficit), it is possible that the majority of recruited patients will have relatively mild impairment as the whole test battery and the additional electrophysiological examinations might be viewed as strenuous, particularly for severely affected patients. Thus, the data set might be biased towards less affected patients. However, some of the clinical tests and the neuroimaging are part of the usual stroke work-up anyways, and the additional clinical and electrophysiological tests are designed to be executed with a minimal amount of active participation. Thus, we assume that we will be able to collect sufficient data of severely affected stroke patients, in order to draw generalizable conclusions from the study findings.

Whereas the collection of the primary data set in the stroke units is relatively straightforward, it might be more difficult to encompass the rehabilitation process, which is heavily influenced by motivation of the patient and support by relatives. Therefore, we invested a lot of effort in creating items for documenting these aspects of the rehabilitation process by a questionnaire capturing these potentially influencing factors. Hence, we assume we will be able to gather a comprehensive data set of the rehabilitation process.

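### Acute tests may be missing because the patient was too unwell, and the imputation methods named as candidates would not, used alone, carry that information into the prediction model

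*Protocol article*

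**What the plan says.** Under 'Participant timeline' the Protocol article ties acute testing to the patient's state. For the first day, "the first clinical tests will be conducted adapted to the patient’s fitness"; for 49–96 h, "Adapted to the patient’s fitness, clinical tests, EEG and motor evoked potentials (MEPs) will be performed". It does not say whether a test is then shortened, postponed or left out. 'Eligibility criteria' admits patients who cannot consent themselves, through a legal representative.

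The missing-data paragraph under 'Statistical methods' says that "algorithms will be tested with artificial data sets including sets with missing data" and then: "Effective algorithms such as nearest neighbors imputation [43] or multivariate imputation [44] on simulated data-sets with missing data will be used as candidate-algorithms". It does not say how the artificial gaps will arise, and it names no indicator or category for a test that could not be performed. Earlier in the same section, the analysis is limited to participants with complete data, with the 90-day examination or death given as part of that.

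'Data management' describes a warning when a value is missing. It mentions no field for the reason.

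**The concern.** A blank for the BDI, SS-QOL, AST, Bells test, DILA-S, EEG or MEP may mean that the patient was too drowsy, aphasic or frail to be tested. Such a blank plausibly says something about prognosis. Nearest-neighbour and multivariate imputation, in standard form, fill it from relations seen in patients whose values were recorded, and the filled value then enters the model like a measured one. Unless an indicator is added, the lasso cannot distinguish an untestable patient from a testable one with the same routine scores.

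At stake is calibration in the group that the Discussion is most concerned to represent. The plan's own performance measure is held-out explained variance, which can hide a bias confined to a minority of patients.

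**Working it through.** **No figure to reproduce.** The article gives no missing rate, no correlation between routine scores and the optional tests, and no SD for the endpoint. All of these are assumed below.

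**Which predictors can be missing.** Initial FM-UE cannot: FM-UE ≤ 50 is an entry criterion, and initial FM-UE is in both the numerator and the denominator of the primary endpoint. NIHSS, mRS, BI, MRI or CT and the blood sample are marked in Table 2 as usual work-up, so they should be present for most patients. That leaves EEG, MEP, Bells test, AST, BDI, SS-QOL and DILA-S, and possibly ARAT and grip strength.

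**Simulation model** (200 training and 4,000 test patients, 150 repeats):
- Severity S is standard normal.
- Two always-recorded scores, each r·S + √(1−r²)·e, with r = 0.5, 0.7 or 0.9.
- Four optional tests, each 0.85·S + √(1−0.85²)·e, missing together.
- Endpoint y = 50 − 20·S + 15·e. SD = √(20² + 15²) = 25 percentage points.
- P(missing) = 1/(1 + exp(1.9 − 2D)), about 24% overall. D is either S itself or the standardised mean of the two recorded scores.
- Gaps filled by 5-nearest-neighbour (kNN) or regression imputation. A ridge linear model stands in for the lasso.

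Mean prediction error (predicted minus true, percentage points) in patients with missing tests, and held-out R²:

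| Missingness driven by | r | Method | Error, no indicator | R², no indicator | Error, with indicator | R², with indicator |
|---|---|---|---|---|---|---|
| Severity itself | 0.5 | kNN | +12.15 | 0.42 | +0.50 | 0.51 |
| | 0.5 | regression | +11.74 | 0.44 | +0.45 | 0.52 |
| | 0.7 | kNN | +7.42 | 0.51 | +0.30 | 0.54 |
| | 0.7 | regression | +6.82 | 0.52 | +0.30 | 0.54 |
| | 0.9 | kNN | +2.38 | 0.58 | −0.03 | 0.58 |
| | 0.9 | regression | +1.92 | 0.59 | −0.08 | 0.59 |
| Recorded scores only | 0.5 | kNN | +0.87 | 0.48 | −0.06 | 0.47 |
| | 0.5 | regression | +0.13 | 0.49 | +0.04 | 0.49 |
| | 0.7 | kNN | +0.70 | 0.52 | −0.11 | 0.52 |
| | 0.7 | regression | +0.02 | 0.53 | −0.04 | 0.53 |
| | 0.9 | kNN | +0.59 | 0.58 | +0.05 | 0.58 |
| | 0.9 | regression | +0.18 | 0.59 | +0.05 | 0.58 |

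In SD units, the kNN errors under severity-driven missingness are 12.15/25 = 0.49, 7.42/25 = 0.30 and 2.38/25 = 0.10.

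**The bias cancels in the overall mean.** At r = 0.5 with kNN, testable patients are under-predicted by 3.79 points, and 0.24 × 12.15 − 0.76 × 3.79 = 2.92 − 2.88 = 0.04. Average calibration would look perfect.

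**Variants with unmeasured frailty** (standardised effect on outcome 0, 0.2 and 0.4, also assumed):
- Eight optional tests, 20% of values missing, 10-neighbour imputation and lasso: one variable for the share of tests not possible raised held-out R² by 0.014, 0.065 and 0.134.
- Four always-observed severity scores, which is nearer to what this study records: the R² change was only about 0.00, 0.01 and 0.045. Over-prediction in untestable patients was still 0.07, 0.22 and 0.35 SD, and the indicator removed nearly all of it.

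In the last variant, at a frailty effect of 0.2, R² moves by 0.01 while the subgroup bias is 0.22 SD. Explained variance alone would miss this.

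**The case against.** The strongest reply is that nothing here is settled. The algorithms are candidates on an open list, to be tried first on simulated data, and an analysis plan that is not shown may add indicators. This is right as far as the modelling goes. It does not cover the reason for a missing test, which has to be noted at the bedside and cannot be recovered later by an analysis plan.

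Four further points limit the concern, and all stand.
- Adapting to fitness need not mean omission. The one concrete example is a 21-channel instead of a 64-channel EEG in severe stroke, and the Discussion says that "the additional clinical and electrophysiological tests are designed to be executed with a minimal amount of active participation".
- Inability to move is usually scored, not missing: SAFE and ARAT have a zero, and an absent motor response is MEP−.
- A reader might take the remark that "the additional electrophysiological examinations might be viewed as strenuous, particularly for severely affected patients" as a forecast of missing tests. In context it explains why recruited patients may be mostly mild; it concerns entry to the study. The same mechanism could cause gaps after enrolment, but the article does not say so.
- Read literally, the complete-data rule would exclude untestable patients rather than impute their values. The missing-data paragraph would then have little to do, so imputing predictors is the more coherent reading, but the article does not say which is meant.

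A reader might also infer that the plan throws away a predictor that it already holds. A blank field would show that a value is missing, but nothing shows that the cause is recorded.

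**Conclusion.** The point holds conditionally. Some acute tests may not be done because of the patient's condition, and the candidate imputation methods used alone would not carry that fact into the model. Whether this matters depends on how much unfitness says about outcome beyond FM-UE, NIHSS, mRS, BI and imaging. Under the assumed inputs, over-prediction in untestable patients is below 1 percentage point if recorded scores explain the missingness. If severity itself drives the missingness, it is about 2 to 12 points, depending on how closely the recorded scores track severity. With four recorded scores the effect on explained variance is small, at most about 0.045.

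The stronger reading, that imputation will make severely affected patients look too favourable, is not supported. The methods are not fixed, FM-UE is always observed, and the article contains no missing rates from which a size could be derived. This is a worthwhile, low-cost improvement to an exploratory study, not an error that invalidates its analysis.

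**What to change.** 1. In REDCap, beside the existing missing-data warning, record for each test block (motor tests, EEG, MEP, questionnaires and cognitive tests) whether it was not done because of patient condition or for technical or organisational reasons.
2. Keep the planned imputation and add the 'not done because of patient condition' indicator per block to the lasso candidates. The same information exists for a future patient at the time of prediction, so its use is legitimate.
3. Include severity-dependent missingness in the artificial data sets, and judge the candidate algorithms on calibration in patients with missing tests as well as on explained variance.
4. State that the complete-data rule refers to the 90-day outcome or death, not to the predictors, so that it agrees with the missing-data paragraph and untestable patients are not excluded.

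The cost is one extra field and about four extra candidate predictors, which the lasso can drop. In the tabulated scenarios the indicator never lowered held-out R² by more than 0.01.
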